***Methods***

*Diagnosis and treatment procedures*

Private providers will be trained on how to recognize and distinguish uncomplicated & severe malaria, supplying unit-dose packaged Coartem® to customers with uncomplicated malaria, and administration of rectal artesunate pre-referral treatment and referral for children with severe and complicated malaria. Rectal artesunate will be provided free of charge for children with severe malaria who cannot take oral medication.Shops will be provided with low literacy visual aids to help explain the symptoms, diagnosis, correct treatment of malaria and danger signs. The shopkeepers will explain the pictorial instructions to customers, as well as give instructions on dosing and how to give the drug to the patient.

Private providers in the intervention areas will be trained in use and interpretation of the rapid diagnostic test. Shops will be supplied with RDTs and a placard identifying them as an approved provider of malaria diagnostic tests. Private providers will be allowed to sell the test, at a price determined by pre-intervention willingness-to-pay studies. The age and sex of patient, onset of symptoms and promptness of treatment-seeking, diagnosis (including RDT result, where appropriate), tablets supplied and outcome of treatment will be recorded by dispensers. Drug sellers will also be trained in the preparation of thick blood films for malaria, and a research blood slide will be prepared from all patients being treated with an antimalarial drug (irrespective of use of RDT) for later validation of diagnosis and treatment by microscopy. All drug sellers will be trained on good laboratory practices, proper disposal of sharps etc. Sharps containers will be provided, and collected regularly for correct disposal at the health facility by the research team.

Consent will be obtained from drug shop owners to participate in the trial, and for randomization of shops to receive RDTs.

Patients are free to choose which shops they use, and will be able to choose between outlets that offer diagnostic testing and those that do not, as this service will be openly advertised. Patients seeking treatment for uncomplicated malaria (or fever) from a registered drug shop in the intervention areas will be offered a RDT prior to drug purchase. Verbal consent will be sought from patients accepting the test, to also prepare a blood film from the fingerprick blood sample for the purposes of the research. Patients who decline an RDT test (and patients seeking treatment at registered drug shops in non-intervention areas) will receive presumptive treatment, as per current practice. This outcome (no test) will be recorded and whether an antimalarial was purchased or not.

Community sensitization on the need for treatment of febrile illness within 24 hrs after onset of illness will also be carried out. Sensitization meetings will also aim to increase awareness of ACTs within the community, the need for better diagnosis, and the importance of adherence to treatment.

*Referral mechanism of severe malaria and non-malarial fevers*

Severe malaria: Children with danger signs consistent with suspected severe malaria (WHO definition 2000) will be given pre-referral treatment using a rectal artesunate suppository and referred immediately to the nearest health unit for further treatment. Patients will be referred using an emergency referral form, including details of symptoms and the use of pre-referral treatment. Shops will keep a dated register for referrals and copy of the referral form with personal identifiers (also at health units).

Non-malarial fevers: By law, registered class C drug shops are not permitted to stock antibiotics or other “prescription only” medicines. Commercial drug sellers will therefore also be trained to examine and refer febrile patients with fever (axillary temperature >37.0OC and a negative RDT (i.e. non-malaria) to the nearest health facility for examination and treatment by a fully qualified health worker, where appropriate. Any patient with danger signs and/or a temperature >38.5OC and a negative RDT should be referred to the nearest health unit as an urgent case. This additional temperature criterion is based on the WHO definition of hyperthermia and is intended to help ensure that those with severe bacterial infections are seen at a health unit. These patients will also be referred using the emergency referral form, which includes details of symptoms and the use of prior treatment. Shops will keep a dated register for referrals and copy of the referral form with personal identifiers (also at health units).

Shopkeepers will be trained to advise RDT negative patients with fever (axillary temperature ≥ 37.0OC) or other symptoms to seek treatment at the nearest health facility for further evaluation by a fully qualified health worker. A standard referral form will be provided to the patient for this purpose. Where no other symptoms are present, the patient will be advised on tepid sponging, but to return for further assessment at the drug shop or a health facility should the symptoms persist or worsen.

To minimise the risk of inadvertent exposure to ACTs during pregnancy, drug sellers will be trained to administer and RDT test, and to refer RDT-positive pregnant women (or women that suspect they may be pregnant) to a health facility for examination by a midwife prior to antimalarial treatment.

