### RDTs have recently been introduced into government health facilities in Uganda. Government health staff in the study area will therefore receive additional supportive training to use RDTs and to only provide treatment with Coartem® after a positive result. The study will ensure that public health facilities are well stocked with RDTs, antimalarials and other essential drugs through the government credit supply system. Community sensitization meetings will be carried out to increase awareness of ACTs, reasons for the new treatment policy for malaria, the need for better diagnosis, and importance of adherence to treatment.

| **Private facilities (pharmacies and drug shops)** |
| --- |
| Drug shops randomised to either:  1) Confirmatory diagnosis with RDTs, followed by sale of a commercially-available ACTs only to those who have a positive RDTs  **or**  2) Current practice:  Presumptive clinical diagnosis and treatment of fever |

*Key strengths to the study site*

- - Multiple sampling points within the same district and health system
  - Study design allows comparison between private and public health care providers to assess patient preferences

This allows direct comparison of the effectiveness of treatment, and the cost-effectiveness of improved diagnosis, in a range of different health care providers within the same country.

*Primary endpoints*

- Proportion of patients receiving appropriate treatment from a commercial drug outlet: % of patients diagnosed with malaria who receive appropriate[[1]](#footnote-2) ACT treatment (irrespective of time since onset of treatment).
- Over-prescription: % of patients, who are not parasite-positive, who receive inappropriate ACT treatment from a commercial drug outlet.
- Provider adherence to RDT result: % of patients who receive appropriate treatment, consistent with RDT result
- Cost-effectiveness of RDT compared to presumptive treatment in home management of uncomplicated malaria.

All endpoints will be examined and reported according to age and sex: children aged 0-4y, 5-15y and adults ≥ 16y. For each age group, the proportion of patients receiving appropriate treatment will be compared between shops with RDTs and shops without RDTs, in order to determine whether diagnostic testing reduces overuse of antimalarials in that age group.

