***Evaluation***

*Appropriateness of treatment and/or referral*

Prescription patterns and drug sales in private shops and clinics will be measured through the use of exit interviews, drug sales records and mystery shopper visits. Drug sales records will be adapted to include data on RDT results. Semi-structured exit interviews will be used to ascertain whether diagnostic testing was offered, was accepted by the patient, and type and quantity of drugs sold. Exit interviews will also investigate the patient’s perception of diagnostic testing and their knowledge and understanding of the test result, treatment advice and/or referral. In non-intervention areas, a finger-prick blood sample will be taken to prepare a research blood film to ascertain by microscopy whether the fever was due to malaria. A random sample of patients will also be followed at home after several days to ascertain adherence to treatment (see section below), outcome of the illness and total household expenditure on treatment. Patients will be recruited on exit from the drug outlet and individual informed consent will be sought from patients (parents or guardians, in the case of minors) to participate in an exit interview and any subsequent household visits.

The appropriateness of treatment provided will be evaluated as the proportion of correctly treated malaria cases, based on the “gold standard” of the research blood slide read by an experienced research technician. Appropriate treatment of fever is a composite definition including both a) those who a slide-positive who are given a 1st-line antimalarial and b) those who are slide-negative who are not given a 1st-line antimalarial. Over-prescription will also be assessed as the proportion of children who are not parasite positive who receive inappropriate ACT treatment.

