### *Sample size requirements*

### Sample size requirements for a cluster-randomised trial15 were calculated for the primary endpoint of the proportion of patients receiving appropriate treatment (in line with parasitological status). Appropriate treatment is defined as a composite including both a) those who are slide-positive who purchase an ACT and b) those who are slide-negative who do not purchase an ACT or other antimalarial drug. As the priority for improving treatment in the private sector is to increase the proportion of true cases that purchase and use an ACT (as opposed to antipyretics only, without any antimalarial treatment), we do not include prompt appropriate treatment within 24 hours as the primary endpoint in this work package.

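### Three unreconciled, arm-dependent rules for the research slide leave intervention patients who decline the RDT and buy no antimalarial without a reference standard, so two primary endpoints are verified differently by arm

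*Protocol*

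**What the plan says.** **Endpoints.** The protocol's Evaluation section (appropriateness of treatment) judges appropriate treatment "based on the “gold standard” of the research blood slide read by an experienced research technician". Under Sample size requirements, one limb of the composite is "those who are slide-negative who do not purchase an ACT or other antimalarial drug". The other limb is slide-positive patients who buy an ACT. Over-prescription, also a primary endpoint, is the percentage "of patients, who are not parasite-positive, who receive inappropriate ACT treatment from a commercial drug outlet". Both endpoints therefore need slides from people who left the shop without an antimalarial.

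**Slide collection.** Three statements govern who gives a slide:

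- Methods, Diagnosis and treatment procedures, on the training of drug sellers: "a research blood slide will be prepared from all patients being treated with an antimalarial drug (irrespective of use of RDT"). It is not limited to one arm.
- The same subsection, on intervention shops: "Verbal consent will be sought from patients accepting the test, to also prepare a blood film from the fingerprick blood sample".
- Evaluation, alongside the exit interviews: "In non-intervention areas, a finger-prick blood sample will be taken to prepare a research blood film".

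**Decliners.** "Patients who decline an RDT test (and patients seeking treatment at registered drug shops in non-intervention areas) will receive presumptive treatment". The protocol also foresees that some will buy nothing: "This outcome (no test) will be recorded and whether an antimalarial was purchased or not". It mentions no slide for them.

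**The concern.** Whether a patient has a reference-standard result depends on the arm, on accepting the RDT and on buying a drug. The last two are affected by the intervention, and buying a drug is part of the outcome itself. Missing slides are then not a random loss, and the loss differs by arm.

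The three statements also leave field staff to decide which one applies. Different readings give different denominators for the same endpoint, so the estimated effect could change with the reading followed. A slide that was never taken cannot be recovered in the analysis. The SAP could only exclude or impute such patients.

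**Working it through.** **Inputs from Sample size requirements.** The baseline ACT purchase rate is 50%. The targets are 75% of RDT-positive and 20% of RDT-negative patients treated.

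**The plan's own figure.** With p0 = 0.50, p1 = 0.75, m = 61, k = 0.25, 90% power and two-sided 5% (the protocol does not state sidedness):

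c = (1.960 + 1.282)² × [0.25/61 + 0.1875/61 + 0.25² × (0.50² + 0.75²)] / 0.25² = 9.74

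This rounds to the stated 10 clusters per arm. The sample size does not depend on the slide rules.

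**Assumptions not in the protocol.** Positivity p is 30–70%. RDT refusal d is 20–40%. Half of decliners are treated. Refusal and decliners' treatment do not depend on slide status. RDT and slide agree. Every antimalarial sold is an ACT. Control patients sampled at exit are representative.

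**Who has a slide**

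| Patient | Treated-patient rule alone | All three rules together |
|---|---|---|
| Intervention, accepts RDT, treated | yes | yes |
| Intervention, accepts RDT, untreated | no | yes |
| Intervention, declines, treated | yes | yes |
| Intervention, declines, untreated | no | **no** |
| Control, treated | yes | yes |
| Control, untreated | no | yes, at exit |

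**Treated-patient rule alone.** Every slide-negative patient with a slide was treated, so over-prescription is 100% in both arms by construction. The composite becomes the slide-positive share of treated patients, which is a different quantity. At p = 0.30 with no refusal:

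- Intervention: 0.3×0.75 / (0.3×0.75 + 0.7×0.20) = 0.225/0.365 = 61.6%, against a true 0.225 + 0.7×0.80 = 78.5%.
- Control: 0.15/0.50 = 30%, against a true 50%.

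**All three rules, composite.** Accepters score A = 0.75p + 0.80(1−p), and decliners truly score 0.50.

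- True = (1−d)A + 0.5d
- Observed = [(1−d)A + 0.5dp] / [(1−d) + 0.5d]

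| p | d | True | Observed | Shift (points) |
|---|---|---|---|---|
| 0.30 | 0.20 | 0.728 | 0.658/0.90 = 0.731 | +0.3 |
| 0.30 | 0.40 | 0.671 | 0.531/0.80 = 0.664 | −0.7 |
| 0.50 | 0.20 | 0.720 | 0.670/0.90 = 0.744 | +2.4 |
| 0.50 | 0.40 | 0.665 | 0.565/0.80 = 0.706 | +4.1 |
| 0.70 | 0.20 | 0.712 | 0.682/0.90 = 0.758 | +4.6 |
| 0.70 | 0.40 | 0.659 | 0.599/0.80 = 0.749 | +9.0 |

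The control arm stays at 50% on this reading, so each shift carries straight into the arm difference. The sign changes because the missing patients are appropriately untreated in a proportion 1−p, which may lie above or below the rate seen in the rest of the arm.

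**All three rules, over-prescription, d = 0.30.** This is calculated among slide-negatives, so positivity drops out.

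- True: 0.7×0.20 + 0.3×0.50 = 0.29
- Observed: (0.14 + 0.15) / (0.70 + 0.15) = 0.29/0.85 = 0.34
- Only accepters have slides: 0.20

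Against 50% in control, the reduction would read 16, 21 or 30 points for the combined, true and accepters-only cases. On the combined reading this endpoint always moves against the RDT arm, because every missing slide-negative patient was untreated. At higher positivity the composite moves the other way.

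**The case against.** The strongest reply is that the statements are cumulative. The first says that all treated patients give a slide. It does not say that untreated patients give none. Accepters give a film from the RDT finger-prick, and control patients, who have no such prick, give one at exit. This is a natural reading and it closes most of the gap. The uncovered group may also be small: if 20% refuse and 90% of those are treated, it is 0.2×0.1 = 2% of the arm. What remains is that untreated decliners have no slide under any reading, and that no passage says the rules are to be added together.

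A reader might infer that the trial is biased towards the RDT arm. That follows if intervention slides come solely from accepters. At 50% positivity the composite would then read 77.5% against a true 72.0% at 20% refusal (+5.5 points), or 66.5% at 40% (+11 points). The documents do not support this as the general case, because the treated-patient rule applies irrespective of RDT use and so gives treated decliners a slide.

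Nor does the protocol say that decliners leave the analysis. They are recorded, and recruitment at exit is not limited to accepters. The analysis population may be set in the SAP, which is not shown. There is also no evidence that who takes the finger-prick affects the slide reading, so nothing here requires the same staff in both arms.

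**Conclusion.** The point holds as an unreconciled collection rule that produces differential verification of two primary endpoints. It is not a demonstrated bias in favour of the RDT arm. On the reading kindest to the protocol, one group is uncovered in the intervention arm, while its control counterpart can be sampled.

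Under the assumptions above, the resulting error in the composite runs from about −0.7 to +9.0 points. The planned difference at 50% positivity with no refusal is 77.5% − 50% = 27.5 points. The error shrinks as refusal falls or as more decliners are treated. Over-prescription at 30% refusal would read about 34% on the combined reading or 20% on the accepters-only reading, against a true 29%. The planning rates are the protocol's. Positivity, refusal and decliners' treatment rate are assumed, so the figures show the range at stake and do not predict the bias. The sample size is unaffected. The rule needs settling before slides are collected.

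**What to change.** Replace the three statements, in Diagnosis and treatment procedures and in Evaluation, with one rule. A research slide is offered, with consent, to every patient recruited at shop exit in both arms, regardless of RDT acceptance or antimalarial purchase. For accepters, the film from the RDT finger-prick may serve. State that patients who decline the RDT are analysed in the arm to which the enumeration area was randomised.

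The exit finger-prick is already planned for control areas, so the cost is revised wording, a consent step and some extra slides in intervention areas. Some people who declined the RDT will also decline this finger-prick, so the gap will shrink but may not close. Recording how many have no slide, by arm, RDT acceptance and purchase, would show what remains.

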### The study will be undertaken in two sub-counties, and census enumeration areas will be randomized to either intervention or control. Registered drug shops located in intervention areas will receive training in the use of rapid diagnostic test for malaria (RDTs) and supplied with RDTs by the research team, and trained to only recommend antimalarial treatment with Coartem® after a positive test result. In the control areas, registered drug shops will continue to dispense antimalarial treatment based on presumptive diagnosis (current practice).

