### *Secondary endpoints*

- Proportion of patients receiving prompt effective treatment from a commercial drug outlet: % of patients diagnosed with malaria who receive appropriate2 ACT treatment within 24 hours of onset of malaria.
- Acceptability of RDTs: % of patients offered a diagnostic test, % of ACT sales preceded by a test
- Perceptions of ACTs and other antimalarial drugs (amongst community; drug sellers; health staff)
- Perceptions and acceptability of malaria diagnosis using RDTs (amongst community; drug sellers; health staff)
- Willingness to offer and perform RDTs to malaria patients (among drug sellers, health workers)
- Patient adherence to prescription (complete dose taken by day 4)
- Referral: Appropriate treatment of RDT negative patients (lack of antimalarial sale and provision of referral); Timeliness and uptake of referral at a health unit by referred patients.
- Coverage of prompt effective treatment: % of patients with fever who received ACT treatment within 24 hours of onset of malaria, measured through household surveys. For comparison with the WHO/RBM indicator in national and international statistics, coverage in children <5 years will be reported separately from older children and adults.
- Source of treatment: % of patients attending health facility for treatment; % visiting a drug shop
- Equity of diagnosis: % of malaria patients receiving a diagnostic test for malaria, across socio-economic groups.
- Equity of treatment: % of patients, who are diagnosed with malaria, receiving treatment with an ACT, across socio-economic groups.

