**To signify agreement to this**

**Type initials of corresponding PI with date:** [name]

**Type initials of lead PI(s)* with date:** [name]; [name]

1. The proportion of correctly treated malaria cases is based on the “gold standard” of a blood slide read by an experienced research technician. Appropriate treatment is a composite definition including both a) those who a slide-positive who are given a 1st-line antimalarial and b) those who are slide-negative who are not given a 1st-line antimalarial (irrespective of dosing). [↑](#footnote-ref-2)

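### The primary composite scores a slide-positive pregnant woman referred untreated, as the protocol orders, as a failure; in practice this happens only in the RDT arm

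*Protocol*

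**What the plan says.** **Referral rules.** Under the heading on referral of severe malaria and non-malarial fevers, repeated under Ethical issues, sellers are trained to test and "to refer RDT-positive pregnant women (or women that suspect they may be pregnant) to a health facility", where a midwife examines them before any antimalarial. Children with danger signs "will be given pre-referral treatment using a rectal artesunate suppository and referred immediately to the nearest health unit for further treatment".

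**Who is tested.** Intervention shops receive RDTs and training in their use. "In the control areas, registered drug shops will continue to dispense antimalarial treatment based on presumptive diagnosis (current practice").

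**Who has a research film.** Patients who accept the test are asked for verbal consent "to also prepare a blood film from the fingerprick blood sample for the purposes of the research". Slides are also planned for everyone treated with an antimalarial, and at exit in non-intervention areas.

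**How the composite scores a slide-positive patient.** The Sample size section credits "those who are slide-positive who purchase an ACT". The Evaluation section credits "those who a slide-positive who are given a 1st-line antimalarial". The footnote to the primary endpoints repeats the first-line wording, with the slide-negative limb being those "who are not given a 1st-line antimalarial (irrespective of dosing"). The headline endpoint asks for ACT treatment from a commercial outlet.

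**Referral as an endpoint.** The one referral endpoint is secondary: "Referral: Appropriate treatment of RDT negative patients (lack of antimalarial sale and provision of referral"), followed by timeliness and uptake among referred patients.

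**The concern.** The protocol requires an act for safety and then scores that act as a failure. The pregnancy rule is triggered by a positive RDT, so although it names no arm it can operate only where RDTs are supplied. A control seller who sells an ACT to the same woman, which is the exposure the rule is meant to limit, is credited with a success. A seller who follows the safety rule lowers the RDT arm's score on the primary endpoint, and the control arm has no matching loss.

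At stake is the adult comparison, which the protocol says will be made separately from the two child age groups. Correct handling of these women is also judged nowhere else, because the appropriateness part of the referral endpoint is limited to RDT-negative patients.

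A lesser, related point is that a slide-positive child given rectal artesunate and referred has not purchased or received an ACT, and so fails under the ACT wording. This can happen in either arm.

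**Working it through.** **1. Scoring of each patient, handled as the protocol directs**

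| Patient | RDT shop | Control shop |
|---|---|---|
| Slide-positive woman, possibly pregnant (RDT-positive if tested) | Referred untreated: failure under every wording | Treated presumptively: success if sold an ACT |
| RDT-positive, slide-negative woman, possibly pregnant | Referred untreated: success | No test; failure if sold an ACT |
| Slide-positive child with danger signs | Rectal artesunate and referral: failure under the ACT wording, arguable under the undefined term first-line antimalarial | Same |

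**2. The protocol's own figure**

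Inputs from Sample size requirements: 50% against 75%, k = 0.25, m = 61 per cluster, 10 clusters per arm, 90% power; 5% two-sided is assumed.

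V = p0(1-p0)/m + p1(1-p1)/m + k²(p0² + p1²)

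Clusters = (1.960 + 1.282)² × V / (p1-p0)² = 10.507 × 0.05795 / 0.0625 = 9.74, rounded up to 10. The stated figure reproduces. (A version that adds one cluster gives 10.74, so 11.)

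**3. Composite without mis-scoring**

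Let q be the share of slides that are positive. It is not in the documents; I assume 50%, range 30-70%. The RDT-positive and RDT-negative targets are applied to slide status.

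- Control: p0 = 0.50 at any q.
- RDT arm: p1 = 0.75q + 0.80(1-q) = 0.775 at q = 50%, a difference of 27.5 points.
- Power = Φ(√(10/V) × |p1-p0| - 1.96). With V = 0.06012 this is Φ(12.90 × 0.275 - 1.96) = 94.4%.

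**4. Pregnancy referrals, RDT arm, adults**

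Let s be the share of slide-positive adults who are referred as possibly pregnant. It is not in the documents; I assume 1-10%. Then p1 = 0.75q(1-s) + 0.80(1-q), so the loss is 0.75qs.

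| q | s | Loss (points) | Difference (points) | Power |
|---|---|---|---|---|
| 50% | 0 | 0 | 27.5 | 94.4% |
| 50% | 1% | 0.4 | 27.1 | 93.9% |
| 50% | 5% | 1.9 | 25.6 | 91.8% |
| 50% | 10% | 3.75 | 23.75 | 88.3% |
| 30% | 0 | 0 | 28.5 | 95.4% |
| 30% | 5% | 1.1 | 27.4 | 94.2% |
| 30% | 10% | 2.25 | 26.25 | 92.7% |
| 70% | 0 | 0 | 26.5 | 93.1% |
| 70% | 5% | 2.6 | 23.9 | 88.5% |
| 70% | 10% | 5.25 | 21.25 | 81.9% |

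Power drops below 90% at s of about 7.7% (q = 50%), 17% (q = 30%) or 3.6% (q = 70%). With the added-cluster version, the q = 50% figures are 92.0% at s = 0, 88.9% at 5% and 84.8% at 10%.

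**5. Offset from slide-negative women**

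Let RDT positivity among slide-negative women be a fraction f of that among slide-positive women (assumed 0.1-0.3). The gain is 0.75(1-q)sf. At q = 50% and s = 5%, the 1.9-point loss shrinks to 1.7 points (f = 0.1, power 92.1%) or 1.3 points (f = 0.3, power 92.6%).

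**6. Children with danger signs, both arms**

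p0 = 0.50q(1-s) + 0.50(1-q), with p1 as in step 4 and s now the affected share of slide-positive children. At q = 50%, s = 5% gives a difference of 26.9 points and power of 94.3%; s = 10% gives 26.25 points and 94.2%.

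**The case against.** The strongest objection is that this is a choice of estimand and not an error. The headline endpoint measures treatment obtained at a commercial outlet, and a referred woman did not get it there. Analysis exclusions may also be left to an SAP that is not shown. Part of this stands: counting, crediting or excluding her are all possible choices. But the protocol fixes the scoring in several places, and each of them conflicts with its own safety rule in one arm only.

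Other mitigating points also stand:

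- Endpoints are to be reported by age and sex, so the effect is confined to adult women and might be visible there.
- Several conditions must coincide: the woman discloses possible pregnancy, accepts a test that may carry a price, tests positive and is actually referred.
- Appropriate prescription in referred cases is part of a primary objective, though it does not enter the composite.
- RDTs and Coartem are aimed mainly at uncomplicated illness, so few children with danger signs may be recruited at exit. No text excludes them.

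A reader might infer more than the documents support:

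- *That the mis-score carries into cost-effectiveness.* The economic section does not define inappropriate treatment. Elsewhere the protocol uses the term for treating negative patients, and on that usage an untreated slide-positive woman is not counted.
- *That she also fails the RDT-adherence endpoint.* This is one interpretation; the protocol does not say what is consistent with a positive result for a woman it orders to be referred.
- *That every tested patient has a film.* Consent is sought, so some referred women will have no slide.
- *That the trial is underpowered.* The 75% target may already allow for these referrals, in which case planned power is unchanged.

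**Conclusion.** The point holds as a modest, one-sided mis-scoring in the adult comparison, confined to women and running against RDTs. The direction before the offset follows from the text; the size rests wholly on assumed shares. At 50% slide positivity the RDT-arm composite loses about 0.4 to 3.75 points for s of 1-10%. Slide-negative women who are referred untreated and score as successes reduce that loss. A loss of planned power follows only if the 75% target ignores these referrals.

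The severe-child part is minor: it occurs in both arms, has almost no effect on power, and is arguable under the first-line wording. It should not be read as a bias of similar weight. Correction is worthwhile because the endpoint as worded penalises sellers for following the pregnancy safeguard, and because the change is cheap.

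**What to change.** 1. Use one wording of the composite in the Evaluation section, the Sample size section and the footnote. Take women who are or may be pregnant, and children with danger signs at presentation, out of it in both arms. Identify them by the same exit-interview questions, asked by study staff in both arms, and not by what the seller did.
2. Report the composite without the exclusion as a sensitivity analysis. Sellers in RDT shops must raise pregnancy, so self-report at exit may differ by arm.
3. Add to the secondary referral endpoint the percentage of children with danger signs given pre-referral treatment and referred (both arms), and the percentage of RDT-positive women who are or may be pregnant referred before any antimalarial (RDT arm only, descriptive).
4. State in the RDT-adherence endpoint that such a referred woman either counts as handled consistently with the protocol or is excluded.

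No change to the cost-effectiveness analysis is needed on this account.

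**Cost.** Two exit-interview questions and slightly fewer analysed patients. Recruitment of 620 per age group per arm leaves room for 10 exclusions before falling below 610. Keeping 610 means recruiting 610/(1-e), which is 617, 643 or 678 if e = 1%, 5% or 10% are excluded. Without a top-up, 614, 589 or 558 remain (m = 62(1-e) per cluster), and power at q = 50% is 94.4%, 94.3% or 94.2%, against 94.4% for the composite in step 3.
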